# Transcranial Magnetic Stimulation of the Default Mode Network to Improve Sleep in Individuals With Insomnia Symptoms: Protocol for a Double-Blind Randomized Controlled Trial

**DOI:** 10.2196/51212

**Published:** 2024-01-26

**Keywords:** continuous theta burst stimulation, transcranial magnetic stimulation, default mode network, sleep, insomnia, cTBS, randomized controlled trial

## Abstract

**Background:**

Cortical hyperarousal and ruminative thinking are common aspects of insomnia that have been linked with greater connectivity in the default mode network (DMN). Therefore, disrupting network activity within the DMN may reduce cortical and cognitive hyperarousal and facilitate better sleep.

**Objective:**

This trial aims to establish a novel, noninvasive method for treating insomnia through disruption of the DMN with repetitive transcranial magnetic stimulation, specifically with continuous theta burst stimulation (cTBS). This double-blind, pilot randomized controlled trial will assess the efficacy of repetitive transcranial magnetic stimulation as a novel, nonpharmacological approach to improve sleep through disruption of the DMN prior to sleep onset for individuals with insomnia. Primary outcome measures will include assessing changes in DMN functional connectivity before and after stimulation.

**Methods:**

A total of 20 participants between the ages of 18 to 50 years with reported sleep disturbances will be recruited as a part of the study. Participants will then conduct an in-person screening and follow-on enrollment visit. Eligible participants then conduct at-home actigraphic collection until their first in-residence overnight study visit. In a double-blind, counterbalanced, crossover study design, participants will receive a 40-second stimulation to the left inferior parietal lobule of the DMN during 2 separate overnight in-residence visits. Participants are randomized to the order in which they receive the active stimulation and sham stimulation. Study participants will undergo a prestimulation functional magnetic resonance imaging scan and a poststimulation functional magnetic resonance imaging scan prior to sleep for each overnight study visit. Sleep outcomes will be measured using clinical polysomnography. After their first in-residence study visit, participants conduct another at-home actigraphic collection before returning for their second in-residence overnight study visit.

**Results:**

Our study was funded in September 2020 by the Department of Defense (W81XWH2010173). We completed the enrollment of our target study population in the October 2022 and are currently working on neuroimaging processing and analysis. We aim to publish the results of our study by 2024. Primary neuroimaging outcome measures will be tested using independent components analysis, seed-to-voxel analyses, and region of interest to region of interest analyses. A repeated measures analysis of covariance (ANCOVA) will be used to assess the effects of active and sham stimulation on sleep variables. Additionally, we will correlate changes in functional connectivity to polysomnography-graded sleep.

**Conclusions:**

The presently proposed cTBS protocol is aimed at establishing the initial research outcomes of the effects of a single burst of cTBS on disrupting the network connectivity of the DMN to improve sleep. If effective, future work could determine the most effective stimulation sites and administration schedules to optimize this potential intervention for sleep problems.

**Trial Registration:**

ClinicalTrials.gov NCT04953559; https://clinicaltrials.gov/ct2/show/NCT04953559

**International Registered Report Identifier (IRRID):**

DERR1-10.2196/51212

## Introduction

### Overview

The sleep disturbances of insomnia include difficulty falling asleep, staying asleep, or inability to fall back to sleep after premature awakenings, or any combination of these, along with daytime sleepiness and dysfunction. Difficulty falling and remaining asleep affected nearly 30% of the US population, with approximately 20% of the general population experiencing occasional difficulties and an additional 10% meeting the clinical criteria for an insomnia disorder [1]. However, this protocol was conducted during the COVID pandemic, when the prevalence of insomnia symptoms increased to 53% and insomnia disorder prevalence jumped from 10% to 17% [2]. Insomnia symptoms have been linked with poorer health across multiple domains and exacts a high societal cost in the workplace, on the health care system, and on an individual’s and family’s quality of life [3-5]. Moreover, side effects from medications used to manage insomnia increase these factors in some cases. Novel approaches that facilitate sleep are critically needed, and some potential neural mechanisms of insomnia create a viable treatment target [6].

The most widely accepted theory of primary insomnia is the hyperarousal hypothesis, which suggests that problems with sleep initiation and maintenance are due largely to the disruptive effects of somatic or cognitive hyperarousal [7,8]. In particular, cortical hyperarousal can emerge from excessive focus on repetitive negative thoughts, including intensive problem-solving, self-reflective rumination, and worry [9-11]. Subjectively, people who struggle with insomnia often make comments such as “I wish I could just turn my mind off” or “I just keep replaying conversations over in my head.” In fact, one of the major features of insomnia is the tendency toward self-reflective rumination and worry [9,12-15]. This internal dialogue contributes to a cycle of self-referential thought and hyperarousal that appears to hinder sleep onset and maintenance [9,16-18]. In fact, worry and sleep disruptions are associated in the general population [3]. In individuals with insomnia, cortical hyperarousal contributes to difficulty initiating and maintaining sleep [19].

Neuroimaging research has shown that internally focused self-reflective processes of this type tend to activate an interconnected system within the brain known as the default mode network (DMN) [20,21]. Moreover, negative ruminative thinking is associated with changes in DMN connectivity and other brain regions associated with cognitive arousal or negative emotion [22]. Patients with insomnia often show abnormalities in the functioning of the DMN that are consistent with the hyperarousal hypothesis [23-25]. The core nodes of the DMN typically include the medial prefrontal cortex, posterior cingulate cortex, precuneus, and bilateral inferior parietal cortex regions but can also include several ancillary smaller regions, including the hippocampus, medial temporal lobes, and other subcortical structures [26]. Individuals with insomnia disorder tend to have increased resting-state functional connectivity (FC) between spatially segregated nodes of the DMN [27,28]. Increased connectivity and activation of the DMN could contribute to the ongoing self-referential processing and internal dialogue that maintains a hyperaroused state and perpetuates difficulties falling and remaining asleep [27,29]. Individuals with insomnia disorder show greater activation of the DMN compared with healthy controls while viewing word lists associated with past, present, and future worries, particularly when the words are self-referential [29].

Mainstream approaches to treating primary insomnia include cognitive behavioral therapy for insomnia and pharmacologic sleep aids, such as hypnotic sedatives [30-33]. While cognitive behavioral therapy for insomnia often helps to reduce ruminative cognitions and is effective at improving sleep for many individuals, there are many who fail to achieve meaningful benefits [34,35]. Similarly, pharmacologic sleep aids also tend to have modest effect sizes [36] and are often associated with unwanted side effects (eg, daytime drowsiness and memory problems) and health-related morbidities [37]. Various noninvasive neuromodulatory approaches have been shown to improve insomnia symptoms, including repetitive transcranial magnetic stimulation (rTMS) [38]. However, low-frequency rTMS has a cortical inhibition effect that has been shown to improve insomnia symptoms, which may be due to hyperarousal across multiple psychological and physiological domains [39].

The proposed protocol aims to bridge the gap between cognitive and neuromodulatory interventions to facilitate sleep onset and longer maintenance by temporarily inhibiting the brain FC that is associated with cortical hyperarousal and presleep ruminative cognitions. Our proposed approach will involve using rTMS prior to bedtime to briefly disrupt the strength of FC among cortical regions of the DMN. As we propose to inhibit connectivity within the DMN, we will use continuous theta burst stimulation (cTBS), which induces long-term depression of cortical neural firing following a sustained stimulation period of 40 seconds [40]. Thus, we hypothesize that the application of cTBS to an easily accessible node of the DMN will suppress the local neural activity of that node and propagate inhibition throughout the DMN, thereby reducing ruminative thinking and worry prior to sleep onset. Decreased DMN connectivity is expected to improve sleep quality and quantity. An increase in slow-wave and rapid eye movement sleep stages has been proposed as mechanisms of rTMS in increasing restorative sleep in individuals with insomnia, so polysomnography (PSG) parameters are the primary outcome measures in the outlined protocol [41]. This phase 1 clinical trial will be the first study to investigate the effects of cTBS targeted to the left inferior parietal node of the DMN on objectively measured sleep outcomes.

### Research Aims and Hypotheses

This study aims to explore the effects of cTBS on (1) the activation and connectivity of the DMN and (2) sleep outcomes. We hypothesize that modulating the DMN by stimulating a targeted region of the left inferior parietal lobule with a single cTBS administration will decrease FC within the DMN and thereby improve sleep parameters (ie, PSG) relative to an identical sham administration.

### Study Design and Randomization

This phase 1 clinical trial (ClinicalTrials.gov NCT04953559) will be conducted with a randomized, double-blind, sham-controlled, counterbalanced, crossover design. Participants serve as their own controls as they undergo 2 identical study sessions separated by at least 5 days (ie, washout period). Participants and study personnel who interact with the participants will be blind to the specific condition (active cTBS vs sham) the participant receives during each study visit. Using a prespecified, equally balanced, block randomization procedure, participants will be assigned to the order in which they receive active cTBS and sham stimulation conditions. The randomization list will be generated by a computer random number generator, with the constraint that half of the participants of each biological sex will receive sham first and half will receive the active cTBS first. This design will allow us to examine the intraindividual effects of the active cTBS and establish the superiority of active cTBS compared with sham stimulation in improving PSG sleep outcomes.

## Methods

### Study Procedures Overview

The study procedures were completed over 3 separate visits. Screening to determine eligibility and baseline assessments was conducted during visit 1. Eligible participants were asked to wear a wrist actigraph for at least 5 days prior to their first in-laboratory overnight visit (visit 2). Based on a preestablished counterbalanced crossover randomization schedule, participants were then assigned to receive either the active cTBS or sham stimulation for their first overnight visit (visit 2) followed by the alternative intervention during their second overnight visit (visit 3) at least 5 days later. As shown in Figure 1, each in-laboratory session lasted 18 hours, including a 2-hour cognitive testing block, 1 hour of preintervention magnetic resonance imaging (MRI), followed by either active cTBS or sham stimulation, and a postintervention hour of neuroimaging. Participants were then fitted with PSG electrodes and were permitted 8 hours of sleep while undergoing PSG sleep monitoring in the lab. The next morning, participants completed another 2-hour cognitive testing block before being released.

The full study execution takes approximately 38-40 hours with 2-3 hours allocated for baseline screening and enrollment (visit 1) and 18 hours allocated for each overnight visit (visits 2 and 3). Table 1 presents the specific assessment measures administered at each visit.

**Figure 1 figure1:**
[figure not shown]
Overview of the pilot randomized controlled trial study design. Participants first complete a web-based eligibility survey screening for sleep disturbances. Potentially eligible volunteers complete an in-lab enrollment process and baseline assessment (visit 1) at a large Southwestern University medical research center. Participants are then randomized to a stimulation order condition. After at least 5 days with actigraphically measured sleep, participants return for an 18-hour overnight session involving 2 MRI scans and overnight sleep (visit 2) at the medical research center. Depending on their condition assignment order, they either receive active cTBS or sham intervention. Participants then undergo a washout period of at least 5 days that includes actigraphically measured sleep. They then return for an identical overnight visit that involves the alternate intervention condition. cTBS: continuous theta burst stimulation; MRI: magnetic resonance imaging.

**Table 1 table1:** List of study activities and assessments performed during study visits during a pilot randomized controlled trial evaluating the preliminary effectiveness of continuous theta burst stimulation in improving sleep in individuals with reported sleep disturbances.

Study activities and assessments			Baseline screening and enrollment (visit 1)		At home		Overnight visits (visits 2 and 3)
**Screening**							
	Consent form	✓					
	Eligibility screening (TMS^a^, health background, MRI^b^, PSQI^c^, ISI^d^, and ESS^e^)	✓					
	Pregnancy test	✓					
**Covariates**							
	Demographics	✓					
	Anxiety (STAI-S^f^ and STAI-T^g^)	✓				✓	
	Depression (BDI-II^h^)	✓				✓	
	Sleep preoccupation (SPS^i^ and GCTI^j^)	✓				✓^k^	
	Caffeine consumption questionnaire	✓					
	Intelligence (WASI-II^l^)	✓					
	Actigraphy (Phillips Actiwatch)			✓			
	Sleep quality (Sleep diaries)			✓			
**Primary Outcomes**							
	Functional connectivity in DMN^m^					✓	
	Sleep (PSG^n^)					✓	
**Secondary Outcomes**							
	Information processing speed (GNG^o^)					✓	
	Attention (PVT^p^)					✓	
	Verbal memory (CVLT-3^q^)					✓	
	Immediate and delayed memory (RBANS^r^)					✓	
	Self-reported sleepiness (KSS^s^)					✓	
	Mood (VAMS^t^)					✓	
	Side effects (pre- and post-TMS assessment)					✓	

^a^TMS: transcranial magnetic stimulation.

^b^MRI: magnetic resonance imaging.

^c^PSQI: Pittsburgh Sleep Quality Index.

^d^ISI: Insomnia Severity Index.

^e^ESS: Eppworth Sleepiness Scale.

^f^STAI-S: State-Trait Anxiety Inventory-State.

^g^STAI-T: State-Trait Anxiety Inventory-Trait.

^h^BDI-II: Beck Depression Inventory.

^i^SPS: Sleep Preoccupation Scale.

^j^GCTI: Glasgow Content of Thoughts Inventory.

^k^Only GCTI.

^l^WASI-II: Wechsler Abbreviated Scale of Intelligence.

^m^DMN: default mode network.

^n^PSG: polysomnography.

^o^GNG: go/no-go task.

^p^PVT: psychomotor vigilance task.

^q^CVLT-3: California Verbal Learning Task 3.

^r^RBANS: repeatable battery for the assessment of neuropsychological status.

^s^KSS: Karolinska Sleepiness Scale.

^t^VAMS: Visual Analogue Mood Scale.

### Ethical Considerations

All study activities and study personnel were approved by the University of Arizona’s Institutional Review Board (IRB) and by the Department of Defense Office of Human Research Oversight (OHRO) in March 2021 (approval 2007900971). Any protocol amendments and reportable new information were disseminated to both IRB and OHRO. All participant information was deidentified for confidentiality. Participants were compensated 500 dollars via check for their participation in the study if they were fully compliant with the study procedures. The study team maintains dissemination control of the final deidentified data set. Final results will only report cumulative population data to respective regulatory and scientific reporting agencies and along with peer-reviewed publications. Access to the deidentified data set will be available upon request to the principal investigator and in conjunction with proper regulatory requirement.

### Participants and Recruitment

A total of 20 otherwise healthy adults with self-reported sleep disturbances were recruited from the greater Tucson and Phoenix metropolitan areas. Recruitment strategies include flyers posted on community boards, advertisements in local newspapers, sponsored social media posts, and email lists at local universities. Individuals who were recruited from the community were directed to complete a web-based survey in a HIPAA (Health Insurance Portability and Accountability Act)–compliant server. If participants met the initial inclusion criteria, a study member then completed a preliminary phone screening with the participant. Study personnel then scheduled an in-person screening visit for eligible individuals.

### Power Analyses

During the study design, we conducted a power analysis to determine the sample size necessary to compare mean changes in DMN connectivity before and after cTBS using a within-subjects ANOVA approach. From prior cited work on transcranial magnetic stimulation (TMS) and FC, a total sample of 20 was found to have sufficient power to answer the research questions to include analysis of 2 groups (within-subject active and sham), 2 repeated measurements (before and after TMS), and a correlation between the change in DMN activation and sleep outcome metrics [42,43].

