### Primary Outcomes: FC Changes in the DMN

We hypothesize that active cTBS will disrupt the within-network and between-network connectivity of the DMN. This hypothesis will be assessed from a 10-minute resting-state FC scan and analyzed using standard procedures in the CONN (v17f or higher). Standard pipelines for preprocessing will be used. Within-network connectivity will be determined by first conducting an independent components analysis of the intrinsic activation patterns across the brain. Twenty independent components will be extracted. Mean activation clusters from each component will be examined for intercorrelation to determine within-network connectivity. Additionally, between-network, region-to-region, and seed-to-voxel analyses will be conducted to compare changes in FC between the 2 stimulation conditions.

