### Analysis Plan

#### FC Changes to the DMN

First-level whole brain connectivity analyses will be undertaken in CONN for each subject at each of the 4 sessions (ie, active prestimulation, active poststimulation, sham prestimulation, and sham poststimulation). This will result in an FC map for each participant at each session, indicating the magnitude and direction of intrinsic correlation between each seed region (eg, lateral parietal cortex of the DMN) and all other voxels in the brain. For our primary analysis, we will estimate the effects of active cTBS on FC within the DMN using multimodal neuroimaging data including resting state FC. Raw NifTI images will be preprocessed using standard functional preprocessing pipelines in CONN [46].

The first-level connectivity maps will be combined in subsequent second-level analyses in CONN to explore the effects of cTBS stimulation on brain connectivity to include (1) independent components analysis, (2) seed-to-voxel analyses, and (3) region of interest to region of interest analyses [44]. Statistically significant differences in FC of the DMN between sham and active conditions will be the minimal important change to confirm the primary hypothesis. Next, PSG parameters measuring sleep stage duration and onsets, arousals, and awakenings will be added as covariates of FC change from before to after stimulation, comparing sham and active cTBS conditions.

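### The primary connectivity comparison is a valid change-score contrast; adjusting for the pre-stimulation scans would usually be more efficient, by an amount that depends on an unreported correlation

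*Protocol article*

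**What the plan says.** Protocol article, Power Analyses: the sample size was chosen to "compare mean changes in DMN connectivity before and after cTBS using a within-subjects ANOVA approach". The layout is described as "analysis of 2 groups (within-subject active and sham), 2 repeated measurements (before and after TMS"), and "a total sample of 20 was found to have sufficient power to answer the research questions". No alpha, power, effect size, standard deviation or scan-to-scan correlation is given.

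Primary Outcomes: FC Changes in the DMN: "analyses will be conducted to compare changes in FC between the 2 stimulation conditions".

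Analysis Plan, FC Changes to the DMN: each participant contributes four maps ("active prestimulation, active poststimulation, sham prestimulation, and sham poststimulation"), so pre-stimulation FC is available at both visits. The only covariates named for the FC model are sleep parameters, which "will be added as covariates of FC change from before to after stimulation, comparing sham and active cTBS conditions". The confirmation rule is: "Statistically significant differences in FC of the DMN between sham and active conditions will be the minimal important change".

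Pre-stimulation FC is not named as a covariate anywhere. The Abstract mentions ANCOVA, but only for the sleep variables. Study Design and Randomization says that order is randomized, with half of each sex receiving each order, and that the washout is at least 5 days.

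**The concern.** In a 2×2 within-subject layout, the condition-by-time interaction is a one-sample test on a double difference and carries the noise of four 10-minute scans. Because order is randomized and balanced, the active−sham difference in the pre scans has expectation zero if there is no carryover. Subtracting it in full is therefore not needed to remove bias. A regression can use as much of the pre-scan difference as is informative.

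What is at stake is power on the primary outcome of a very small trial. Data Management restricts analysis to participants who completed the study, so 20 is a ceiling. Enrolment closed in October 2022, so the analysis is the main lever left. Confirmation of the hypothesis rests on statistical significance.

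**Working it through.** **Inputs.** From the article: n=20, two within-subject conditions, two scans per visit, randomized balanced order. Assumed, because the article is silent: two-sided alpha 0.05, equal variances of the two differences, and r over a wide range.

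**The plan's own figure.** N=20 cannot be reproduced without an effect size, so it is inverted. For a paired test with 19 df, 20 completers give 80% power at a standardized difference-in-changes of 0.66 and 90% at 0.76. At 0.5 the power is 56%, and 34 participants would be needed for 80%. Normal-approximation check at 0.66: (1.96+0.84)²/0.66² ≈ 18, close to 20 before the t correction.

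**Variance.** Let Dpre and Dpost be the active−sham differences in the pre and post scans, each with variance s² and with correlation r.

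- Change score: Var(Dpost − Dpre) = 2s²(1−r).
- Adjusted: residual Var(Dpost given Dpre) = s²(1−r²).
- Ratio, adjusted to change: s²(1−r²) / [2s²(1−r)] = (1+r)/2.
- Post scans alone: s². Subtraction exceeds this when 2(1−r) > 1, that is, only when r < 0.5.

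**Power at n=20.** Simulation, 20,000 trials per setting, effect set to give 80% power under the change score, sequence (period) term included in the adjusted model:

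| r | (1+r)/2 | simulated ratio | adjusted power |
|---|---|---|---|
| 0 | 0.50 | 0.53 | 97% |
| 0.2 | 0.60 | 0.64 | 94% |
| 0.5 | 0.75 | 0.80 | 88% |
| 0.6 | 0.80 | 0.86 | 86% |
| 0.7 | 0.85 | 0.90 | 83–84% |
| 0.8 | 0.90 | 0.95 | 81–82% |
| 0.85 | 0.925 | 0.97 | 80% |
| 0.9 | 0.95 | 1.01 | 79–80% |
| 0.95 | 0.975 | 1.04 | 78% |

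The simulated ratio exceeds the large-sample one because the slope is estimated from 20 people. From a 50% base, adjusted power is 76–77% at r=0, 59–60% at r=0.5, 50% at r=0.85 and 49% at r=0.95. The adjusted estimate showed bias of about zero, and its type I error was 4.8–5.1%.

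**Equivalent sample size.** In large samples, the change score would need 20/0.50 = 40 participants at r=0, 20/0.75 = 26.7 at r=0.5 and 20/0.95 = 21.1 at r=0.9 to match the adjusted analysis.

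**What r is.** It is not the raw pre–post correlation. With same-visit scan correlation a and cross-visit correlation b, r = (a−b)/(1−b). For a=0.6, b=0.5: 0.1/0.5 = 0.2. For a=0.9, b=0.5: 0.4/0.5 = 0.8. To reach r=0.85 with b=0.5, a must be 0.85 + 0.5×0.15 = 0.925.

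**The case against.** **This is a preference, not an error, and the final model may differ.** The power section explains a sample size. The second-level contrast is not written out, the confirmation rule does not itself say change score, and a full analysis plan may add the adjustment. It stands that the planned test is valid and nothing is misstated. However, the outcome and analysis sections also describe change from before to after stimulation compared between conditions, so the change contrast is what the article sets out.

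**The gain may be small.** The two scans of a visit fall on the same evening, while visits are at least 5 days apart. Same-visit scans could therefore be much more alike, which means a high r. This stands as a limit on the claim, because the article cannot settle r. Against it, the scans are separate 10-minute acquisitions with the participant out of the scanner between them, and r near 0.85 needs a same-visit correlation of at least 0.85 for any non-negative b.

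**Subtraction buys robustness.** If active stimulation left a stable shift c in both visit-3 scans, the double difference cancels it. The regression with sequence is then biased by about −c(1−r)/2, or −0.4c at r=0.2. This is correct. It matters little if carryover is absent, which is plausible: Brief cTBS of the LLP Lobule puts the suppression at around 50 minutes, possibly more, against a washout of days.

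**Cost and timing.** The regression has 17 df against 19, and changing a primary model after enrolment has closed has a credibility cost. Both stand and shape the fix.

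**Conclusion.** The planned FC comparison is valid but generally not the most efficient use of the scans collected. From an 80% base at n=20, adjustment gains about 17 points at r=0, 8 at r=0.5, 4 at r=0.7 and 2 at r=0.8. It gains nothing near 0.85–0.9 and loses about 2 points at 0.95. The possible gain is much larger than the possible loss, but the actual size is unknown because r is not reported.

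A reader might infer three stronger things that the article does not support:

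- That the change-score test is wrong. It is unbiased for the same effect.
- That adjustment is sure to raise power materially. That holds only for low to moderate r.
- That subtraction inflates variance outright. It does so relative to adjustment in large samples, but relative to ignoring the pre scans only when r < 0.5.

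The conclusion assumes two-sided 0.05, equal variances of the two differences, and no carryover into the visit-3 scans.

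**What to change.** For the planned ROI-to-ROI DMN analysis, prespecify, before unblinded second-level results are seen, a regression of each participant's post-scan active−sham difference on the pre-scan active−sham difference plus sequence. Leave the pre-scan difference uncentred and code sequence symmetrically (±½), so that the intercept is the treatment effect. Using the within-subject difference as the covariate keeps between-subject variation in FC out of the slope. Report the change-by-condition contrast alongside it; the voxelwise and component analyses can stay as planned. Report the observed r, so that readers can see how much the adjustment contributed.

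If unblinded results have already been seen, keep the change contrast as planned and present the regression as a labelled sensitivity analysis.

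Cost: exporting ROI values and fitting one regression per planned connection, 17 instead of 19 df, and a stated assumption of no carryover. No new data are needed.
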